### Data analysis

For all continuous outcomes, we will calculate changes from baseline to 12 weeks. For each continuous outcome, we will then conduct two sample *t* tests to determine whether the mean change for that outcome was statistically significantly different for each intervention arm relative to the comparison arm. For all categorical outcomes, we will use chi-square or Fisher’s exact tests to between-arm changes from baseline to 12 weeks. While we will be conducting multiple tests for statistical significance, we will not adjust our threshold for statistical significance (e.g., using a Bonferroni correction) for multiple comparisons so as to avoid making a type II error in this pilot study. We will conduct all analyses using Stata 14.

Semi-structured interviews will be audio recorded and subsequently transcribed verbatim. Interviews will then be imported into qualitative analysis software. Two investigators will independently read and code transcribed interviews. Interviews will then be coded jointly using consensus conferences. Interviews will be analyzed using directed content analysis [53].

Consistent with a mixed-methods sequential explanatory design [40], we will integrate (i.e., connect) the quantitative and qualitative findings in the final stage of data analysis. In this way, we will interpret our quantitative data in the context of qualitative participant experience.

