### Allocation

Individuals who meet study inclusion criteria and consent to study participation will be randomized using a web-based tool, the University of Michigan computerized randomization system (TATUM—Treatment Assignment Tool-UM), which allows for blinded treatment allocation. We will use stratified randomization with variable block lengths to ensure a balance of age and gender between groups. Recruitment and randomization will be ongoing until we have 35 individuals in each arm of the study.

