### Outcome measures

#### Primary outcome measures

The primary outcome will be change in autonomous motivation to prevent T2DM. Autonomous motivation will be measured using the seven-item, validated Treatment Self-Regulation Questionnaire at baseline and 12-week follow-up [42].

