### Sample size

Based on prior studies of autonomous motivation among University of Michigan employees [34], we anticipate that the baseline level of autonomous motivation to prevent T2DM among Premier Care or Grad Care members who decline DPP participation will be 5.7 (measured on a 1 to 7 scale with 1 being the lowest and 7 being the highest). During the 12-week intervention period, we anticipate that autonomous motivation will increase by 0.6 points in the JOOL-only arm and by 0.8 points in the JOOL-plus arm. Assuming a standard deviation of 1.0 for change in autonomous motivation in both arms, 29 participants in each arm will provide 80% power to detect these changes in autonomous motivation in the intervention arms compared to the comparison arm. Prior research demonstrates that a 0.5-point increase in autonomous motivation can lead to greater weight loss and increased physical activity compared to individuals who did not achieve this increase in autonomous motivation [36]. To account for the possibility that some participants may be lost to follow-up during our 12-week intervention, we have conservatively inflated our sample size by 20% to enroll 35 participants in each arm.

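### The primary outcome is tested by an unadjusted t test on change, which is valid but less precise than a model using the baseline score and strata already collected

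*Protocol article*

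**What the plan says.** The Data analysis section of the protocol article sets one rule for every continuous outcome: "For all continuous outcomes, we will calculate changes from baseline to 12 weeks". It follows this with two-sample t "tests to determine whether the mean change for that outcome was statistically significantly different for each intervention arm relative to the comparison arm". No baseline covariate and no stratum term is named.

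The primary outcome falls under this rule. Autonomous motivation is scored with the "validated Treatment Self-Regulation Questionnaire at baseline and 12-week follow-up". The Allocation section says: "We will use stratified randomization with variable block lengths to ensure a balance of age and gender between groups".

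The Sample size section expects that "autonomous motivation will increase by 0.6 points in the JOOL-only arm and by 0.8 points in the JOOL-plus arm". It works from "Assuming a standard deviation of 1.0 for change in autonomous motivation in both arms" and concludes that "29 participants in each arm will provide 80% power to detect these changes in autonomous motivation". The expected baseline mean is 5.7 on a 1 to 7 scale.

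**The concern.** A t test on change subtracts the baseline with a coefficient of exactly 1. That coefficient is optimal only if the slope of the 12-week score on the baseline score really is 1. With an expected mean of 5.7 on a scale that ends at 7, there are only 1.3 points of headroom on average. People who start high have little room to rise, so a slope below 1 is likely. The change score then over-corrects: it adds noise and keeps part of any chance baseline difference between arms.

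Age and gender are used to form the randomisation strata but are then dropped. If they predict outcome, the t test's standard error is larger than it needs to be.

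What is at stake is precision in a trial of 35 per arm whose Data analysis section declines multiplicity adjustment in order to avoid a type II error. The chosen test works against that aim, although the data needed for a sharper one are already planned.

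**Working it through.** **Inputs from the protocol (Sample size).** SD of change 1.0; differences 0.6 (JOOL-only) and 0.8 (JOOL-plus); 29 evaluable and 35 enrolled per arm.

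**Assumptions, because the article does not give them.** Two-sided 0.05; no mean change in the comparison arm, and the same SD there; equal variances at the two visits; baseline to 12-week correlation ρ of 0.3 to 0.8.

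**Step 1: the protocol's own figure under its own test.** The standard error of the difference is 1.0 × √(2/29) = 0.263.
- JOOL-only: noncentrality 0.6/0.263 = 2.28 on 56 df, power 61%.
- JOOL-plus: 0.8/0.263 = 3.05, power 85%.
- If all 35 per arm complete, JOOL-only reaches 70%.

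The stated 80% is therefore not reproduced for JOOL-only against comparison. A one-sided test at 0.05 with 29 per arm gives 73%. An omnibus three-group F test with means 0, 0.6 and 0.8 gives 80.3% at 29 per arm, but that is not the planned test.

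**Step 2: the effect of adjusting for baseline.** Let s² be the variance at each visit.
- Var(change) = 2s²(1 − ρ) = 1, so s² = 1/[2(1 − ρ)].
- Residual variance after regression on baseline = s²(1 − ρ²) = (1 + ρ)/2.
- Equivalent gain in sample size = 2/(1 + ρ).

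Power for 0.6 by the noncentral t, taking off three degrees of freedom for baseline, age and gender:

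| ρ (assumed) | Residual SD | Power, 29 per arm | Power, 35 per arm | 2/(1 + ρ) |
|---|---|---|---|---|
| t test on change | 1.000 | 61% | 70% | 1.00 |
| 0.3 | 0.806 | 79% | 87% | 1.54 |
| 0.5 | 0.866 | 74% | 81% | 1.33 |
| 0.7 | 0.922 | 68% | 76% | 1.18 |
| 0.8 | 0.949 | 66% | 74% | 1.11 |

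These rows credit the baseline covariate only; nothing is added for age and gender.

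**Step 3: carry-over of chance imbalance.** With equal variances the slope equals ρ. A baseline difference D between arms shifts the change-score difference by (ρ − 1)D. The standard error of D at 29 per arm is s√(2/29), so an imbalance of one standard error shifts the estimate by (1 − ρ)s√(2/29) = √[(1 − ρ)/2] × 0.263 in absolute size:
- ρ = 0.3: 0.16 points
- ρ = 0.5: 0.13 points
- ρ = 0.7: 0.10 points
- ρ = 0.8: 0.08 points

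On the 0.6 target, these are about 26%, 22%, 17% and 14%. The adjusted model removes this component.

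**Step 4: the strata alone.** If age and gender explained 2% to 10% of the variance of change, power for 0.6 at 29 per arm would move from 63% to between 64% and 67% (normal approximation, which gives 63% where the noncentral t gives 61%). The documents do not say how well they predict change.

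**The case against.** The strongest reply is that this is a preference about efficiency. Under randomisation the t test on change is unbiased, and leaving out prognostic strata makes it conservative, not invalid. The test matches the quantity on which the sample size rests, the SD of change. The trial is a pilot, and a separate analysis plan may add an adjusted analysis. All of that stands except as a reason to leave the text alone: the article names the main test outright, so it can be judged as a choice.

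Four stronger readings are tempting, and the documents do not support them:

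- **That the analysis ignores the baseline.** It does not. A change score uses it, with the slope fixed at 1, and only (slope minus 1) times an imbalance carries over.
- **That the primary analysis as a whole lacks power.** Only JOOL-only against comparison falls short. That shortfall comes from the sample-size statement, not from the choice of a change score.
- **That adjustment restores the stated 80%.** At 29 per arm it comes close only when ρ is about 0.3.
- **That the chi-square or Fisher tests cannot use a person's baseline answer.** The Data analysis section applies them to changes from baseline, so this criticism does not fit the text.

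The size of the gain is also uncertain. No correlation is given. A real ceiling at 7 would make equal variances and a constant treatment effect only approximate.

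**Conclusion.** The point holds as a recommended improvement to a valid analysis. For the primary outcome and the other continuous outcomes measured in all three arms, the stated test is less precise than one using data already in hand.

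Under the assumptions listed, power for the JOOL-only difference at 29 per arm rises from 61% to between 79% and 66% as the assumed correlation goes from 0.3 to 0.8. The direction of the gain is secure under equal variances; its size is not, because the correlation is unknown. Most of it comes from the baseline covariate, and the strata may add little.

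The point does not extend to categorical outcomes. Nor does it extend to outcomes collected only in JOOL users or only in JOOL-plus: no three-arm comparison exists for these, and their baseline is the first two weeks of the intervention, after randomisation.

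**What to change.** For the primary outcome and each continuous outcome measured at baseline and 12 weeks in all three arms:

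1. Make the main analysis a linear model of the 12-week value on arm (three levels), the baseline value of the same outcome, and the stratification factors age and gender.
2. Report the adjusted difference for each intervention arm against comparison with a 95% confidence interval.
3. Keep the two-sample t test on change as a sensitivity analysis.

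This changes analysis wording only and needs no new data. It costs about three degrees of freedom if age enters as one term; the number of age strata is not given, so the exact count is an assumption.

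Separately, restate the power in the Sample size section for each pairwise comparison under the test actually planned. Adjustment alone should not be offered as the remedy for the JOOL-only shortfall.

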## Abstract

**Background:**

Rates of participation in Diabetes Prevention Programs (DPPs) are low. This may be due, in part, to low levels of autonomous motivation (i.e., motivation that arises from internal sources and sustains healthy behaviors over time) to prevent type 2 diabetes (T2DM) among many individuals with prediabetes. Mobile health (mHealth) technologies that incorporate principles from the Self-Determination Theory offer an effective and scalable approach to increase autonomous motivation levels. One promising mobile phone-based application is JOOL Health, which aims to help users connect certain health behaviors (e.g., sleep and diet) with personal values in specific life domains (e.g., family and work). The first aim of this study is to estimate whether JOOL Health can increase autonomous motivation to prevent T2DM among individuals with prediabetes who declined DPP participation. The second aim of this pilot study is to examine the intervention’s feasibility and acceptability.

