We propose a pilot study to estimate the ability of JOOL Health—used alone and also in conjunction with Fitbit devices (i.e., activity tracker and wireless internet-enabled scale)—to increase autonomous motivation to prevent T2DM among individuals with prediabetes who declined participation in a formal DPP (i.e., DPP non-participants). Given that JOOL Health draws on SDT to inspire behavioral change, we hypothesize that autonomous motivation to prevent T2DM will increase to a greater degree among individuals who use JOOL Health compared to individuals who only receive written educational materials about T2DM prevention. Because Fitbit devices can also enhance user motivation by fostering autonomy, competence, and relatedness (through sharing of fitness data) [38]—key SDT tenets of psychological need—we also hypothesize that autonomous motivation to prevent T2DM will increase to a greater degree among individuals who use JOOL Health in conjunction with Fitbit devices compared to individuals who use the JOOL Health application alone. Further, we aim to examine the feasibility of recruiting DPP non-participants and the acceptability (adherence and qualitative experience as reported during semi-structured interviews) of the intervention. We hypothesize that recruiting DPP non-participants may have unique challenges, as these individuals have already declined to participate in one lifestyle intervention. However, as compared to the DPP, this is a low-intensity intervention, which may appeal to individuals seeking a less time-consuming program, and we believe that study participants will find the intervention acceptable. Taken together, these data will inform the design and implementation of a larger trial to test the effect of JOOL Health on clinically relevant outcomes, including weight loss, physical activity, and DPP engagement.

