## Discussion

Evidence-based Diabetes Prevention Programs are available in communities across the USA and can effectively promote weight loss among individuals with prediabetes [12]. However, the DPP alone may be insufficient to improve population health, as low rates of participation limit the program’s reach. Prior studies have described determinants of participation [17] and non-participation [16, 54, 55] in lifestyle-change programs, as well as barriers to adherence among those who initially engage in these programs [19]. However, it is unknown whether interventions to increase levels of autonomous motivation—a key driver of lifestyle change among individuals with prediabetes [25]—can promote healthy behaviors and greater rates of DPP engagement among individuals with prediabetes.

In this pilot study, we aim to test whether JOOL Health can increase autonomous motivation among individuals with prediabetes when used alone and also in conjunction with other mHealth tools. Because changes in individuals’ levels of autonomous motivation occur early along the path to behavioral change, we anticipate a large effect size from the intervention and will therefore have the power to detect between-group differences in this outcome in the context of a relatively small study (*N* = 105). This will serve as an important indicator that a larger study may lead to measurable changes in clinically relevant health outcomes such was body weight, physical activity, and DPP engagement. It is also possible that we will not detect changes in autonomous motivation. For this reason, we will conduct qualitative interviews with study participants so that we can interpret our quantitative findings in the context of individual-level participant experiences. For example, it is possible that some individuals may desire additional support (e.g., brief counseling, nutritional advice, explicit exercise goals) to augment the JOOL Health experience. Some individuals may want more tailored messaging from the JOOL Health application while others may find the daily charting to be burdensome. Understanding participants’ experiences will enable us to refine and strengthen our program. In this way, we will tailor our intervention to better meet the individual-level needs of this previously overlooked population with prediabetes who have not engaged in a formal DPP.

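### The first hypothesis concerns all JOOL users, but only arm-by-arm tests are planned and no contrast is assigned to it; the stated 80% power is also not met for JOOL-only (about 61%)

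*Protocol article*

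**What the plan says.** The protocol article frames the question in two ways.

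- **JOOL as a whole.** The Abstract says: "The first aim of this study is to estimate whether JOOL Health can increase autonomous motivation". The first hypothesis in Background expects a larger rise in autonomous motivation "among individuals who use JOOL Health compared to individuals who only receive written educational materials about T2DM prevention". Both JOOL arms receive the app (Study design, Intervention), so this wording covers both. The devices have their own second hypothesis, a larger rise "among individuals who use JOOL Health in conjunction with Fitbit devices compared to individuals who use the JOOL Health application alone".
- **Arm by arm.** The sentence in Background that opens the statement of the study's purpose, ahead of both hypotheses, sets out JOOL Health by itself and JOOL Health with Fitbit devices as separate uses. The Discussion repeats this: the aim is to "test whether JOOL Health can increase autonomous motivation among individuals with prediabetes when used alone and also in conjunction with other mHealth tools".

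Data analysis plans, for each continuous outcome, two-sample t tests of whether "the mean change for that outcome was statistically significantly different for each intervention arm relative to the comparison arm", without multiplicity adjustment. No combined contrast appears.

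Sample size anticipates that "autonomous motivation will increase by 0.6 points in the JOOL-only arm and by 0.8 points in the JOOL-plus arm", assumes an SD of change of 1.0, and states that "29 participants in each arm will provide 80% power to detect these changes in autonomous motivation" relative to the comparison arm. Enrolment is then raised to 35 per arm to allow for loss to follow-up.

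**The concern.** A hypothesis about all JOOL users needs a named contrast that answers it. The plan has two tests, each using two of the three arms, and no rule linking them to that hypothesis. If one test is significant and the other is not, the authors must choose afterwards how to read the result for the primary outcome.

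The single 80% figure hides a related problem. It is attached to two different anticipated gains with the same SD and the same number per arm, and these cannot both give the same power. If the shortfall falls on JOOL-only, it falls on the one planned comparison that separates the app from the devices. A non-significant result there could be read as evidence against the app when the trial had little more than a 60% chance of detecting the anticipated gain.

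**Working it through.** **Inputs.** From Sample size: 29 completers per arm, SD of change 1.0, gains 0.6 (JOOL-only) and 0.8 (JOOL-plus). From Allocation: equal arms, so JOOL combined against comparison is 58 v 29. Not stated, and assumed here: two-sided 5%, and no change in the comparison arm.

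**Formula.** Power = P(|T| > t_crit), where T is noncentral t with noncentrality δ/SE.

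**1. The plan's own figure (29 v 29).** SE = √(1/29 + 1/29) = 0.2626; 56 degrees of freedom; t_crit = 2.003.

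- JOOL-only: 0.6/0.2626 = 2.285, power **61.2%**.
- JOOL-plus: 0.8/0.2626 = 3.046, power **84.9%**.

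Neither is 80%. A normal approximation gives 62.7% and 86.1%; a one-sided 5% test gives 73.0% and 91.4%. At 29 per arm, 80% two-sided power corresponds to a difference of 0.75. A difference of 0.6 needs about 45 completers per arm (80.4%; 44 give 79.5%).

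**2. Combined contrast, (JOOL-only + JOOL-plus)/2 minus comparison.** δ = (0.6 + 0.8)/2 = 0.7. SE = √(1/58 + 1/29) = 0.2274; 84 degrees of freedom from a three-arm model; t_crit = 1.989. Noncentrality 0.7/0.2274 = 3.078, power **86.0%**.

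**3. How the two arm-wise tests behave together** (simulation, gains 0.6 and 0.8):

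| Event | Share of trials |
|---|---|
| Both significant | about 57% |
| At least one significant | about 89% |
| Exactly one significant | about 32% (89 − 57) |
| At least one significant when there is no effect | about 9% |

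With the false-positive risk of the either-test reading held at 5%, its power falls to about 83%.

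**4. Sensitivity.**

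| Scenario | JOOL-only | JOOL-plus | Combined |
|---|---|---|---|
| Base case, 29 per arm | 61% | 85% | 86% |
| No loss, 35 per arm | 70% | 91% | 92% |
| Both arms gain 0.6 | 61% | 61% | 74% |
| Comparison arm gains 0.2 | 32% | 61% | 58% |

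If only one regimen works, the combined contrast is weak. With gains of 0 and 0.8, δ = 0.4, noncentrality 0.4/0.2274 = 1.759, power about **41%**. With gains of 0.6 and 0, δ = 0.3, noncentrality 0.3/0.2274 = 1.319, power about **26%**.

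**The case against.** The strongest reply is that the planned tests answer an aim the protocol states. The statement of purpose in Background, the Sample size section and the Discussion all treat the two JOOL arms separately, and Data analysis matches them. That stands: the arm-wise tests are not a mistake.

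A reader might infer that the plan throws away power, 86% combined against 61%. The documents do not support this. The 61% is the weaker arm only; JOOL-plus already has 85%, and the two unadjusted tests together have 89% for at least one effect. In a pilot that openly declines adjustment, little is lost by that measure. The qualification is that the either-test reading is nowhere stated as the rule and carries about 9% false-positive risk.

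A reader might also infer that the combined contrast is the app-versus-no-app comparison and should replace the arm-wise tests. It cannot. Half of the combined group also has an activity tracker and scale, whose data feed the tailored messages (Intervention). If the app alone did nothing and JOOL-plus gained 0.8, the combined test would still be significant in about 41% of trials, and crediting the app would be wrong.

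Finally, this is a pilot with an estimation aim and follow-up interviews, disagreement between arms can be informative, and extra contrasts may sit in a SAP that is not shown. This lowers the weight of the point. It does not remove it: the article itself states the hypothesis, the tests and the 80%, and these do not fit together.

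**Conclusion.** The point holds in a limited form. The first hypothesis is worded for JOOL users as a whole and no contrast is mapped to it, while the arm-wise tests answer an arm-wise objective that is also stated. About one trial in three would give a split result, with no stated reading for that hypothesis. Separately, the 80% in Sample size is not delivered for JOOL-only on the plan's own inputs.

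These sizes rest on 29 completers per arm, SD 1.0, the anticipated gains, and the two assumptions the document does not state (two-sided 5%, no change in the comparison arm). If the comparison arm also improves, all three powers fall, and the combined contrast then has no advantage over JOOL-plus. The case for adding it is that it answers the hypothesis as worded with one prespecified 5% test. It is not uniformly more powerful, and making it the sole test of the first aim would be a trade-off that the documents do not justify.

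**What to change.** **Data analysis.** Fit one model with all three arms for change in autonomous motivation. Report three contrasts, each with a 95% CI: JOOL-only minus comparison, JOOL-plus minus comparison, and (JOOL-only + JOOL-plus)/2 minus comparison. Name the third as the contrast for the first hypothesis as worded. State that it estimates the average effect of JOOL with or without devices, and that only JOOL-only against comparison isolates the app. The two arm-wise contrasts keep their present standing.

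**Sample size.** Replace the single 80% with the power for each contrast: 61% (JOOL-only), 85% (JOOL-plus) and 86% (combined). State the assumptions beside them, including significance level, sidedness and the change expected in the comparison arm.

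**Cost.** A few sentences and one contrast statement; no extra participants or data. The price is interpretive: the combined estimate averages two regimens and performs poorly if only one works, which is why the arm-wise contrasts must be reported with it.
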